# Efficacy of dapagliflozin in the treatment of HFrEF with obstructive sleep apnea syndrome (DAHOS study): study protocol for a multicentric, prospective, randomized controlled clinical trial

**DOI:** 10.1186/s13063-023-07332-x

**Published:** 2023-05-09

**Keywords:** Heart failure, Dapagliflozin, Sleep apnea, Sleep-disordered breathing

## Abstract

**Background:**

Heart failure with reduced ejection fraction (HFrEF) is associated with sleep dyspnea (SDB), which plays an adverse role in the pathophysiology of the condition. SDB management in HFrEF, however, remains controversial. HFrEF’s medical management has recently made significant progress with the discovery of new therapeutic avenues, namely sodia-glucose cotransporter-2 (SGLT-2) inhibitors, and better treatment of co-morbidities. Dapagliflozin, one of the SGLT-2 inhibitors, is a good candidate for correcting SDB of HFrEF patients because their known mechanisms of action are likely to counteract the pathophysiology of SDB in HFrEF.

**Methods/design:**

The trial is a 3-month, multicentric, prospective, randomized controlled clinical study. Patients (i.e., adults with left ventricular ejection fraction ≤ 40%, Apnoea–Hypopnoea Index ≥ 15) will be randomized to receive optimized heart failure therapy plus a standard dose of dapagliflozin, while the control group will receive only optimized heart failure therapy. Patients will be evaluated before and after 3 months (nocturnal ventilatory polygraphy, echocardiography, laboratory testing, and quality-of-life and SDB questionnaires). The primary outcome is the change in the Apnoea–Hypopnoea Index, before and after 3 months of treatment.

**Trial registration:**

www.chictr.org.cn, ChiCTR2100049834. Registered 10 August 2021.

## Background

Heart failure (HF) refers to the end stage of various structural or functional diseases of the heart [1]. An estimated 64.3 million people are living with heart failure worldwide [2]. In developed countries, the prevalence of known heart failure is generally estimated at 1 to 2% of the general adult population [3]. A high proportion of patients with heart failure combined with sleep dyspnea accounts for 50–75% of the total number of patients with heart failure [4, 5]. Sleep apnea is a disease characterized by interrupted breathing at night, easy arousal, daytime sleepiness, and reduced blood oxygen saturation. It is mainly divided into central sleep apnea syndrome (CSAS) and obstructive sleep apnea syndrome (OSAS) [6, 7]. Patients with sleep disordered breathing (SDB) suffer from repeated hypoxia due to interrupted or weakened breathing during sleep, which causes sympathetic nerve excitation and impairs the function of vascular endothelium, thus affecting the cardiovascular system of the patients. Patients with heart failure combined with sleep apnea who did not receive further treatment had twice the risk of death as those without SDB, which was mainly associated with an increased incidence of malignant ventricular arrhythmias [8]. In patients with concomitant ischemic cardiomyopathy, untreated consequences are more severe, with a threefold increase in mortality [9, 10]. Currently, obstructive sleep apnea has been identified as a risk factor for heart failure and exacerbation.

At present, the treatment of chronic heart failure has made a milestone progress. Despite this, 1 ~ 2% of adults in the world still suffer from heart failure, with a high incidence rate, and the resulting hospitalization rate, fatality rate, and social and economic burden also increase year by year [11]. Dapagliflozin, a SGLT-2 inhibitor, was found to have a unique role as a hypoglycemic agent in the treatment of heart failure, especially in patients with reduced ejection fraction. DAPA⁃HF was a multicenter, prospective randomized controlled trial involving 4744 patients with chronic heart failure (LVEF < 40%) from 20 countries, of whom 2605 (54.9%) were non-diabetic, 1097 (23.1%) were Asian, and 237 (5.0%) were from China. Results showed that dapagliflozin was associated with a significant reduction in the primary composite end point compared with placebo [12]. Dapagliflozin is clearly indicated in the domestic label for use in adult patients with heart failure (HFrEF) in patients with reduced ejection fraction (NYHA II-IV) to reduce the risk of cardiovascular death and hospitalization due to heart failure [13, 14].

Dapagliflozin has also been shown to be effective in patients with sleep apnea and diabetes. From the mechanism, it is not difficult to guess that dapagliflozin may have a potential effect of improving the ventilation of OSAHS patients. In recent years, it has been partially verified in some studies. For type 2 diabetes patients complicated with obstructive sleep apnea (OSA), dapagliflozin not only improves blood glucose, blood pressure, blood lipids, and weight loss but also improves ventilation function better than glimepiride [15]. In Yi Tang’s case control study [16], 36 newly diagnosed patients with T2 diabetes who also had OSA were randomly assigned to two groups. The effects of dapagliflozin can be significant in decreasing blood glucose, body mass index, blood pressure, and blood pressure AHI, improving hypoxemia during sleep, and reducing excessive daytime sleepiness, so it has the potential to be an effective treatment for OSA. A prospective, open-label, single-arm, multicenter trial showed improvement in moderate to severe SDB as well as mild SDB [17].

Few studies have reported the pharmacological treatment of sleep apnea especially with heart failure [18–20]. We hypothesized that dapagliflozin, as a new star in the treatment of heart failure, could improve sleep apnea in heart failure patients. In our study, patients with heart failure complicated with moderate to severe OSA (AHI equal or greater than 15) [21] and reduced ejection fraction were enrolled, and dapagliflozin was added to the conventional optimized heart failure treatment group. This is to observe and evaluate the changes of OSAH-related indicators and the treatment of heart failure and verify the role of dapagliflozin in the treatment of heart failure complicated with OSA.

## Methods/design

### Study design

This study is a prospective, multicenter, randomized controlled superiority trial. The study will be conducted in two research centers (Zhongda Hospital and Jinling Hospital). This paper presents the design and protocol for the trial according to the Standard Protocol Items: Recommendations for Interventional Trials (SPIRIT) statement [22].

An overview of the study design and timeline for participants is provided in Fig. 1. Those eligible for dapagliflozin treatment and treated in real-life conditions will be invited to participate. Following the inclusion and exclusion criteria, a pre-therapeutic evaluation will be conducted [physical examination, echocardiography, laboratory testing, Minnesota Living with Heart Failure Questionnaire and EuroQol Group 5-Dimension Self-Report Questionnaire (EQ-5D), Epworth Sleepiness Scale, nocturnal ventilatory polygraphy] [20].

**Fig. 1 Fig1:**
[figure not shown]
Study design overview

Patients will be divided into two groups:Group 1: patients received optimized heart failure therapy plus dagaglizin 10 mg daily, dapagliflozin will be started the day after the polygraphyGroup 2 (control group): patients received only optimized heart failure therapy

“Optimal drug therapy” in large heart failure trials usually refers to a combination of BBL, ACE inhibitors or ARBs and MR antagonists, with an optimal dose [23]. After 3 months of treatment, the final evaluation will include physical examination, echocardiography, laboratory testing, Minnesota Living with Heart Failure Questionnaire and EQ-5D, Epworth Sleepiness Scale, and nocturnal ventilatory polygraphy for all patients included in the study. During the research process, the participants cannot take other types of SGLT2 inhibitors such as empagliflozin and canagliflozin. Using ventilators to treat sleep apnea is not allowed; if it is necessary, they will withdraw from the study.

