### Follow-up and duration of the study

There will be two visits at the clinical research center, one before (baseline) and one after (3 months follow-up) the dapagliflozin intervention. Data collection to assess efficacy of the intervention will be managed by research team members. An overview of the measures used at each of the four time points is illustrated in Table 2. For improving the compliableness of patients, the strategies are as follows: (1) adhere to the principle of voluntary participation and explain the benefits of this study to the participants and the importance of treatment and adherence to the treatment. Health education process could increase the related knowledge, change the behavior, and enhance the compliance of patient. (2) Written informed consent will be obtained from each patient before they begin the trial. All participants will fill in informed consents. (3) The treatment is free for participants, such as the relevant examination expenses and the telephone bill, traffic expenditures, and analgesic drugs incurred during the treatment and follow-up. (4) Record participants’ contact methods in detail, including mobile phone, WeChat, and e-mail for contact and follow-up.

**Table 2 Tab2:** Administration of study measures by assessment period

Research phase	Screening and randomization	Treatment period		
Interview	1	2	3	4
Research date	− 7–0	28 ± 2	56 ± 4	84 ± 6
Baseline information				
Informed consent	●			
General information	●			
History	●			
Physical examination	●	●	●	●
Treatment				
Inclusion/exclusion criteria	●			
Combined medication	●	●	●	●
Compliance		●	●	●
Completion of research				●
Inclusion/exclusion criteria				
PSG	●			
Echocardiography	●			
Security index				
Blood routine	●			●
Urine routine	●			●
Blood biochemical	●			●
Electrocardiogram	●			●
Adverse event assessment		●	●	●
Outcome				
AHI	●			●
Epworth Somnolence Scale (ESS)	●	●	●	●
Echocardiography	●			●
NT-proBNP	●			●
Quality of life as measured by the Minnesota Living with Heart Failure Questionnaire	●	●	●	●
EQ—5D—3L				
L_SpO2_	●			●
Inflammatory factors	●			●

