### Outcomes

#### Primary outcome

The primary endpoint of the trial is the AHI change determined by nocturnal polygraphy, before and after 3 months of treatment with dapagliflozin. The 2012 American Academy of Sleep Medicine recommendations are used to characterize apnea and hypopnea events, the phenotype, whether central, obstructive, or mixed.

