### Adverse events

The adverse events will be investigated by open questions, including general symptoms, and by specific questions regarding symptoms potentially related with the drugs used in the trial, as hypotension, frequent urination, urgent urination, fatigue, loss of appetite, nausea, vomiting, etc. The rate of adverse effects will be determined by comparing the frequency of adverse events in the experimental group and control group. The criteria for discontinuing the trial for an individual participant are as follows:Those who have serious adverse reactions in the study and are not suitable to continue to participate in the studyDuring the study period, the participants had other acute and severe diseases and needed to take emergency measures

(The reasons and time of withdrawal from the study will be recorded in detail. Participants who have exceeded 1/2 of the course of treatment will be included in the curative effect analysis.)

Researchers will do their best to prevent possible dangers caused by this study. If adverse events occur, the medical expert committee will identify whether they are related to drug treatment or research process. The project will provide treatment expenses and corresponding economic compensation for the damage related to the trial in accordance with the Criterions for the Quality Control of Clinical Trial of Drugs.

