### Statistical methods

Outcomes will be analyzed by intention-to-treat and per-protocol. A low attrition rate is expected, since the interventions are of short duration and minimal risk. Missing data will be considered as missing. Data imputation will not be employed. Normally distributed data will be presented as means and standard deviation. Non-normally distributed data will be displayed as median and interquartile range. The significance of the differences between two groups will be tested by chi-squared test for categorical variables and t test for measurement data. Results with a *P* value lower than 0.05 for alpha error will be considered statistically significant. Statistical analyses will be performed using the SPSS 26.0 software (SPSS Inc., Chicago, IL, USA). We will do an interim analysis when the number of patients reaches half that.

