## Discussion

As a result of untreated OSA, hypertension, cardiovascular disease, metabolic disorders, and neuropsychiatric problems can be significantly worsened [29]. As a result of periodic airway collapses, OSA causes sleep fragmentation and intermittent hypoxia. These phenomena lead to an increase in oxidative stress, reactive oxygen species formation, increased inflammation via the NF-kB pathway [30], sympathetic activation [31], metabolic dysregulation, and endothelial dysfunction [32] resulting in insulin resistance [33], hypertension, and cardiovascular diseases.

In patients with symptomatic OSA, positive airway pressure (PAP) is the primary treatment option. Treatment of OSA with PAP has some limitations. Patient adherence is reported to be poor with an averagemask use of 4.4 h/night [34]. Additionally, CPAP therapy has a limited effect on blood sugar control. There are currently no pharmacological agents listed in the treatment protocols for OSA, and medication use is restricted to the prevention and correction of precipitating conditions such as obesity and hypothyroidism [35, 36]. There is growing evidence that SGLT-2 inhibitors may reduce OSA severity [16, 17, 37, 38]. SGLT2 inhibitors may benefit patients with OSA by promoting weight loss. OSA severity can be improved by reducing weight and reducing diet alone. This effect is facilitated by SGLT2 inhibitors by increasing lipolysis and decreasing central obesity [38, 39]. As fat deposits around the neck and thorax may worsen upper airway collapsibility, weight loss may have a beneficial effect on airway collapse and AHI. However, the meta-analysis by Mir et al. included 65 patients with OSA and T2DM, and showed that AHI, BMI, and systolic blood pressure (SBP) all decreased and SpO_2_ increased with SGLT2 inhibition, though these results were not statistically significant [40].

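### Patients who come to need a ventilator for sleep apnoea leave the study with no post-baseline AHI scheduled and no imputation, so an outcome-related event removes them from the primary comparison

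*Protocol article*

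**What the plan says.** In the Study design section, below Fig. 1, the protocol article states: "Using ventilators to treat sleep apnea is not allowed; if it is necessary, they will withdraw from the study". The consequence is withdrawal from the study, not only from study treatment. Nothing there says what makes a ventilator necessary. The final evaluation at 3 months ends with "and nocturnal ventilatory polygraphy for all patients included in the study".

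On the outcome: "The primary endpoint of the trial is the AHI change determined by nocturnal polygraphy, before and after 3 months of treatment with dapagliflozin". Follow-up and duration of the study says: "There will be two visits at the clinical research center, one before (baseline) and one after (3 months follow-up) the dapagliflozin intervention". Table 2 lists four interviews but marks AHI only at the first (day -7 to 0) and the fourth (day 84 ± 6). It has no column for an early-withdrawal assessment.

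Statistical methods says: "Outcomes will be analyzed by intention-to-treat and per-protocol". It also says that missing data stay missing, that nothing is imputed, and that measurement data are compared by t test.

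Adverse events gives two criteria for discontinuing an individual: a serious adverse reaction that makes continuing unsuitable, and a second under which "the participants had other acute and severe diseases and needed to take emergency measures". Ventilator use for sleep apnoea is in neither. A parenthesis says that the reason and time of withdrawal are recorded, and adds: "Participants who have exceeded 1/2 of the course of treatment will be included in the curative effect analysis".

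**The concern.** Sleep apnoea judged to need ventilation is close to being a poor result on the primary outcome. It is also a plausible event here: everyone enters with AHI of at least 15 events/h, and the Discussion says "In patients with symptomatic OSA, positive airway pressure (PAP) is the primary treatment option". A rule that removes such patients before the only follow-up AHI makes loss depend on the outcome. A complete-case t test then compares two selected groups, whatever the analysis set is called.

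The Discussion acknowledges that the trial has neither double blinding nor placebo. With no stated criterion, the judgement that ventilation is necessary can differ between arms. With 30 patients planned, a handful of such losses can move the estimate. The responder outcomes have the same problem: patients who are plausibly treatment failures drop out of the denominator.

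**Working it through.** **1. One patient followed through the document.** Suppose a ventilator becomes necessary on day 30 or on day 60.

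- Study design: the patient is withdrawn from the study.
- Table 2: the next scheduled AHI is day 84, so no post-baseline AHI is due before withdrawal.
- Statistical methods: nothing is imputed, so there is no AHI change to enter in the t test and no responder status.
- Adverse events: half of an 84-day course is 84/2 = 42 days. If the half-course sentence covers this withdrawal, the day-60 patient belongs in the efficacy analysis and the day-30 patient is not covered by it. No AHI value is named for the day-60 patient, and as scheduled none exists.

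**2. The plan's own figure.** Inputs from Sample size: difference 8, SD 6 events/h, no change in controls, power 90%, alpha 5% (taken as two-sided), 20% loss; 1:1 allocation from Randomization process.

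n per arm = 2 × (1.960 + 1.282)² × 6² / 8² = 11.8, rounded up to 12. Then 12/0.8 = 15 per arm, or 30 in total. The stated 30 is reproduced. A t test with 15 per arm and no losses has 94% power.

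**3. Expected difference under outcome-related removal.** Assumptions: AHI change is normal with SD 6, mean 0 in controls and -8 on dapagliflozin, and every patient whose AHI rises by more than c is removed. The values of c are not in the documents; they are shown as a range.

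With z = (c - μ)/6, the proportion removed is 1 - Φ(z) and the mean of those left is μ - 6 × φ(z)/Φ(z). For c = 6:

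- Controls: z = 1, mean = -6 × 0.2420/0.8413 = -1.73.
- Dapagliflozin: z = 14/6 = 2.33, mean = -8.16.
- Difference: 8.16 - 1.73 = 6.43.

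| c (events/h) | Controls removed | Treated removed | Control mean | Treated mean | Difference |
|---|---|---|---|---|---|
| +6 | 15.9% | 1.0% | -1.73 | -8.16 | 6.43 |
| +8 | 9.1% | 0.4% | -1.08 | -8.07 | 6.99 |
| +10 | 4.8% | 0.1% | -0.63 | -8.03 | 7.40 |

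Against a true 8, these are about 20%, 13% and 7.5% too small.

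**4. Simulation check** (100,000 trials, 15 per arm, t test on completers). At +6 the difference is 6.42 and power 85%. At +12 it is 7.68 with power 93%. At +3 it is 5.41 with power 72%.

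**5. Direction.** The same simulation, removing the worst one, two or three patients from one arm only:

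| Arm losing patients | True difference | 1 removed | 2 removed | 3 removed |
|---|---|---|---|---|
| Control | 8 | 7.27 | 6.61 | 6.03 |
| Dapagliflozin | 8 | 8.75 | 9.38 | 9.96 |

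With no true effect, removing the worst one, two or three from one arm raises the rejection rate from 5% to about 7%, 11% and 16%.

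**The case against.** Several points on the other side have force.

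- **No flat contradiction.** A reader might infer that Adverse events gives a different rule for the same patients. It does not name ventilator users, and its half-course sentence concerns who is analysed, not who is withdrawn. A patient can be withdrawn and still analysed. What stands is that its list omits the trigger in Study design, and that its half-course rule has unclear scope and names no AHI value.
- **Polygraphy at withdrawal is not excluded.** The article nowhere says that a recording is withheld, and early-termination procedures may be in the full protocol. That no AHI is taken is inferred from the schedule. The withdrawal rule and the bar on imputation, however, are stated, and together they produce the loss unless something else is added.
- **The removal model is an assumption.** No AHI criterion for ventilation is given, and no interim AHI is scheduled that would reveal a rise. Symptoms, baseline severity or preference could prompt ventilation. A reader might infer that the worst AHI courses are certain to be removed; the documents make this likely but do not say so.
- **Frequency and direction are unknown.** With rare events the effect is small, as the +12 threshold shows, and it reverses if treated patients are the ones lost.
- **AHI recorded on a ventilator.** A reader might infer that a day-84 AHI suppressed by ventilation would be counted as improvement. The article provides for no such recording, so no size is put on it here.

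**Conclusion.** The point holds in limited form. Followed as written, the article removes patients from the primary comparison and the responder proportions for a reason closely related to the outcome, on an unblinded judgement without a stated criterion. Intention-to-treat does not bring them back, because they have no follow-up AHI and nothing is imputed. Study design, Adverse events and Statistical methods do not together say how these patients enter the analysis and must be reconciled.

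If losses fall mainly on controls, the planned difference of 8 is estimated as 6.4 to 7.4 events/h for assumed thresholds of +10 down to +6. If they fall mainly on treated patients, the effect is overstated. These figures rest on normal AHI changes with the plan's SD of 6, on the assumed removal rule, and on a frequency that the documents do not give. The point should be corrected; it does not invalidate the design.

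**What to change.** Change measurement and analysis only. Whether and when to ventilate, and the on-treatment rules, stay with the clinicians.

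1. For a patient who is to start a ventilator, bring the planned final polygraphy and questionnaires forward to before ventilation where feasible, and use that AHI in the intention-to-treat comparison.
2. Do not use an AHI recorded on the ventilator as the outcome.
3. Continue collecting the other scheduled data on these patients.
4. Count them as non-responders in the 20% and 50% outcomes. State openly that this treats the event differently from the AHI comparison: a patient could have a fall of 25% before ventilation and still count as a non-responder.
5. Report ventilator starts by arm, with reason and time.
6. State one rule, consistent across Study design, Adverse events and Statistical methods, for how these patients enter each analysis, including whether the half-course sentence applies to them.

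The cost is protocol wording and moving a recording that is already planned, for those patients only. The sample size of 30 does not change. The drawback is that their AHI is taken earlier than 3 months. Enrolment was still under way when the article was submitted, so the change could help patients not yet at their final visit at that time.
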